A total of 105 patients will undergo a physical frailty assessment before (T1) and after 5 days (T2) of dexamethasone administration (6 mg/m^2^ per day in 3 dosages). A subset of 50 children will be assessed at 3 additional timepoints (T3, T7, and T11), to observe the process of sarcopenia and physical frailty longitudinally. This subset comprised children participating in the DexaDays-2 randomized controlled trial based on the severity of their neurobehavioral problems. These 50 patients will receive physiological dosages of hydrocortisone or placebo during a 5-day dexamethasone treatment, and the cross-over will take place after 2 courses of dexamethasone treatment. The sample size is based on the DexaDays-2 study power calculation [40].

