### Potential Determinants

We will explore the following potential determinants for the components of sarcopenia and physical frailty: sex, age, weight Z-scores at diagnosis, time since the start of treatment, registered toxicity and serious adverse events in induction therapy, cumulative vincristine dosage, dexamethasone pharmacokinetics, and carrier of relevant genetic variants (candidate single-nucleotide polymorphisms). Information regarding these factors will be extracted from the electronic patient files or is collected in the DexaDays-2 study. Dexamethasone kinetics are measured through peak levels (2-3 hours after the first dexamethasone administration on day 1 of the dexamethasone course) and trough levels (measured on day 6, at least 12 hours after the last dexamethasone dose administered on the previous evening). A peripheral blood sample to extract germline DNA, for evaluation of carrier status of relevant candidate single-nucleotide polymorphisms related to sarcopenia and physical frailty, is taken on T1 as part of the DexaDays-2 study. As a complete array (Illumina GSA) will be run, we will be able to select the most relevant specific additional single-nucleotide polymorphisms of interest, based on evidence from the most recent literature (Figure 1).

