### Statistical Analysis

The results of the physical frailty assessments, that is, SMI, handgrip strength, self-reported fatigue, walking speed, and physical activity (component scores), will be reported as means and SDs, or as median and interquartile ranges if data are non-normally distributed. The frequency of sarcopenia and physical frailty, as well as the individual components at all timepoints will be reported in percentages and schematically visualized. A correlation matrix will be built to explore coherence between the additional measure TRF and the other frailty components.

To evaluate the potential change in frailty components after 5 days of dexamethasone administration, a paired Student *t* test or Mann-Whitney *U* test will be used depending on the distribution of the data.

To evaluate whether the mean scores from the frailty components change between T1, T3, T7, and T11, 1-way ANOVA will be employed.

To study the effect of dexamethasone administration at T1, T3, T7, and prior to T11 on sarcopenia, physical frailty, and each individual components, generalized mixed models will be estimated. These models incorporate correlations between repeated responses on the same individual. Patient-specific random intercept, age, weight, time since the start of therapy, and cumulative vincristine dosage will be included in the model.

Multivariable linear regression model will be estimated to investigate associations between the potential determinants (patient- and treatment-related factors, pharmacokinetics, and genetics) and the assessment scores at T1 and T2 (SMI, handgrip strength, self-reported fatigue, walking speed, TRF, and physical activity). Results will be presented as regression coefficients along with 95% CI.

Multivariable logistic regression models will be estimated to explore associations between the aforementioned potential determinants and the occurrence of sarcopenia and physical frailty at T1 and T2. Odds ratios along with 95% CIs will be estimated.

Statistical analyses will be performed using software packages R Statistics (version 1.0.143; R Foundation) and SPSS (version 26.0.0.1) for Windows (IBM).

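### The planned multivariable logistic models have too few events for their parameters, so maximum-likelihood odds ratios will be moderately inflated; Firth estimation with SNPs entered singly would correct this cheaply

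*Protocol article*

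**What the plan says.** The Statistical Analysis section of the protocol article plans multivariable logistic models to "explore associations between the aforementioned potential determinants and the occurrence of sarcopenia and physical frailty at T1 and T2", reported as odds ratios with 95% confidence intervals. It names no penalisation and no limit on the number of predictors.

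The Potential Determinants section gives the list: "sex, age, weight Z-scores at diagnosis, time since the start of treatment", then "registered toxicity and serious adverse events in induction therapy, cumulative vincristine dosage, dexamethasone pharmacokinetics, and carrier of relevant genetic variants (candidate single-nucleotide polymorphisms". Pharmacokinetics is more than one variable: "Dexamethasone kinetics are measured through peak levels", taken after the first dose of the course, and also through trough levels on day 6. The genetic item is plural, and the section allows further variants to be chosen from a full array.

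On numbers, Study Design and Patient Recruitment states: "A total of 105 patients will undergo a physical frailty assessment before (T1) and after 5 days (T2) of dexamethasone administration". It adds: "The sample size is based on the DexaDays-2 study power calculation". The cohort was therefore not sized for these models.

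**The concern.** Maximum-likelihood logistic regression with few events per parameter gives log odds ratios that are on average too far from zero. When an outcome or a carrier group is rare, some data sets separate and yield no finite estimate.

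The definitions make a large event count unlikely to be guaranteed. Sarcopenia requires low muscle mass and low strength together, and frailty requires at least three of five components. The article gives no expected prevalence for either.

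At stake is the size of the reported associations. The Discussion hopes that exploring determinants may help to recognise vulnerable children earlier, and inflated odds ratios would make some determinants look stronger than they are. Accrual is complete, so the sample cannot grow. Only the estimator and the set of predictors can still change.

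**Working it through.** **Inputs from the article.** N = 105 at most, before any missing assessments. The article's own N cannot be reproduced, because its inputs lie in the parent trial.

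**Parameter count, with one SNP.**
- T2: sex, age, weight Z-score, time since start, toxicity/serious adverse events, cumulative vincristine, peak level, trough level, one SNP = 9. It is 10 if toxicity and serious adverse events are separate terms, and more with further SNPs.
- T1: this assessment precedes the course, whereas the peak is drawn 2-3 hours after the first dose and the trough on day 6. Without these two, the count is 9 − 2 = 7.

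**Ceiling on events per parameter.** Whatever the prevalence, the smaller outcome class is at most 52 (half of 105, rounded down).
- T2: 52/9 = 5.8
- T1: 52/7 = 7.4

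At prevalence p (50% or less) with k parameters, events per parameter = 105 × p / k.

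**What this does to the estimates.** Prevalence and effect sizes are assumptions. The main simulation used N = 105, nine predictors (three binary), true odds ratios of 2, 2 and 1.5 with the rest null, and 1,500 data sets per row. Results are for a continuous predictor with true odds ratio 2 per SD, fitted by maximum likelihood:

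| Prevalence | Events per parameter | Bias of log OR | Median OR | Non-finite fits | 95% CI coverage |
|---|---|---|---|---|---|
| 10% | 10.5/9 = 1.2 | +31% | 2.31 | 9.7% | 94% |
| 20% | 21/9 = 2.3 | +20% | 2.25 | 0.5% | 93% |
| 30% | 31.5/9 = 3.5 | +15% | 2.19 | 0% | 94% |
| 50% | 52/9 = 5.8 | +15% | 2.16 | 0% | 95% |

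A further simulation put the bias at about 12% at 50% prevalence and 30% at 10%. With eight parameters, the closest case run to the T1 model, the bias was +22%, +15%, +15% and +13% at 10%, 20%, 30% and 50%.

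**Non-finite fits under less favourable assumptions.** With weaker effects, three correlated predictors and a binary predictor carried by 15%, the share of non-finite fits was 55%, 24%, 9.5%, 3.7% and 0.1% at prevalences of 5%, 10%, 15%, 20% and 50%.

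**Several SNPs together.** With 15 parameters the bias rose to +70%, +35%, +26% and +25% at 10%, 20%, 30% and 50% prevalence. Coverage was 91% to 95%.

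**Firth estimation.** In a separate simulation (nine predictors, one with 15% carriers, true log OR 0.693, 1,500 replicates):
- 15% prevalence: maximum likelihood 0.833/0.693 = 1.20 (+20%); Firth 0.688/0.693 = 0.99
- 20%: 0.810/0.693 = 1.17 (+17%); Firth 0.689/0.693 = 0.99
- 30%: 0.789/0.693 = 1.14 (+14%); Firth 0.691/0.693 = 1.00

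In the main scenario, with 500 data sets per cell for Firth and taking a continuous and a binary predictor together, Firth bias ran from −2% to +9%, against +13% to +32% for maximum likelihood. At 5% prevalence in the less favourable scenario (105 × 0.05, about five events), Firth itself fell short by 10% to 14%.

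**The case against.** **The specification is partly inferred.** The article does not name the estimator or say that every determinant and SNP enters one model. It condenses a fuller plan that may settle both. This stands as a caveat. But a multivariable model on the determinants already listed is most naturally read as joint entry, and unpenalised fitting is the usual meaning when nothing else is named. The point is that the stated method, predictor list and N fit together badly; it is not a complaint about missing detail.

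**The harm is modest.** In a simulation with nine predictors the bias was about one third to one half of the estimator's standard deviation. Coverage was 93% to 95%, and null effects were rejected about 5% of the time. The planned intervals will show the imprecision, and the aim is explicitly exploratory. All of this stands and limits the weight of the point.

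**Stronger readings that the article does not support.**
- A reader might infer that non-finite odds ratios threaten at any prevalence. In the main simulation none occurred at 30% or 50%.
- A reader might infer that these odds ratios alone will decide which children are called at risk. The Discussion speaks only of a possibility arising from exploring determinants generally, and linear models on the component scores are planned as well.
- A reader might want either time since start or cumulative vincristine dropped for collinearity. The article gives no figure for their correlation, and collinearity widens intervals without biasing the odds ratios.
- A reader might apply the count of nine to T1 as well. That would use levels measured after the outcome.

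**Conclusion.** The point holds in a limited form. The ceilings of 5.8 events per parameter at T2 and 7.4 at T1 need no assumption about prevalence. They rest on joint entry of the listed determinants with one SNP, and missing assessments or more SNPs would lower them.

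The inflation of roughly 10% to 30% on the log odds ratio scale rests on unpenalised fitting and on assumed effects (true odds ratio 2 per SD). It is largest when the outcome is uncommon. Non-finite estimates are a material risk only at about 20% prevalence or less, or with a small carrier group. Interval coverage is close to nominal. This is an avoidable bias in an exploratory analysis and does not invalidate it, but it is worth correcting because the remedy is easy.

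**What to change.** In the Statistical Analysis section:

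1. State that the logistic models are fitted by Firth penalised likelihood with profile-penalised 95% confidence intervals.
2. Enter candidate SNPs one at a time on top of the clinical determinants. With one SNP per model, the count stays at about nine at T2 and seven at T1.
3. Leave the peak and trough levels out of the T1 models and keep them for T2.

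Firth regression is a standard routine in R, which the article already names, and no new data are needed. The cost is slightly shrunken estimates and no mutual adjustment between SNPs. If the outcome proves very rare (about five events), Firth estimates will still be poor, and the results should say so.

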## Results

Patient accrual started in 2018 and was finalized in spring 2021. A total of 105 children undergoing ALL therapy will participate in this study. From autumn 2021 statistical analyses will be performed.

## Discussion

This paper describes the design of the first study on sarcopenia and physical frailty in children during maintenance therapy for ALL. The results of this study will provide information and create awareness on the magnitude and severity of sarcopenia and physical frailty in this specific group of children, which may help us understand which factors are associated with the large variations in physical ability between children receiving similar treatments. With this knowledge we may be able to identify physically vulnerable children at an earlier stage. This is important because being vulnerable to sarcopenia or frailty can complicate continuation of ALL therapy, independence in physical functioning, reaching motor milestones, and participation in daily life activities.

In this study we will assess sarcopenia involving a combination of low muscle mass *and* low muscle strength for the first time in patients with ALL. The SMM will be estimated using the Tanita MC-780 multifrequency segmental body composition analyzer, which is a validated, reliable, low-cost, fast, and non-invasive device to estimate body composition in the pediatric population [43].

None of the previous studies in children with ALL concerning muscle mass loss incorporated functional muscle strength assessments. We expect this to be of additional value because recent updates and consensus definitions state the importance of including muscle function in the concept of sarcopenia [61], as reduced muscle mass in combination with normal muscle strength may suggest malnutrition rather than sarcopenia [62]. Besides, in children, impaired muscle function directly influences motor development and is therefore relevant [63].

To explore this aspect further, we added a functional strength measurement to the assessment: the TRF. Although the handgrip dynamometer is a reliable instrument to measure handgrip strength in children [46], this may not be the first sign of reduction of muscle strength. We suspect that a generalized reduction in muscle strength (such as in sarcopenia and physical frailty) might be better shown by a functional performance test. The time and degree of support needed to rise from the floor are standardized measures to quantify deterioration and are associated with walking ability in children with muscular dystrophy [64].

The results of this study will provide knowledge about the effect of treatment with high doses of dexamethasone on muscle loss and other components of physical frailty, and therefore insights into the severity and risks of these side effects. Furthermore, through exploring potential determinants that could influence the occurrence of the sarcopenia or frailty, we might be able to identify children at risk for substantial problems at an earlier stage. As a result, we might be able to start targeted interventions and clinical studies on reducing the dexamethasone-induced components of physical frailty with, for example, nutrition and exercise.

This study has a number of strong points. First, because care for children with ALL in the Netherlands is centralized, a national cohort of Dutch children can be screened on eligibility for this study, rendering a large and hopefully unbiased population. Second, all children will have a physical frailty assessment by a skilled pediatric physiotherapist or a trained medical doctor, which benefits the validity and reliability of the performed physical assessment. Third, the burden of the study will be minimal because the assessments are performed during maintenance therapy of ALL, in which children experience less toxicities, fewer hospital admissions, and therapy is mainly administered at home and in the outpatient clinic. Fourth, we selected sarcopenia and frailty endpoints in accordance with previous research and the official definitions. Furthermore, we added 1 functional strength measurement, the TRF, based on expert opinion and on particular feasibility in children with ALL.

Some possible study limitations have to be taken into account as well. We will only include children participating in the DexaDays-2 study, which could potentially lead to selection bias, as patients who experience dexamethasone-induced neurobehavioral problems could be more motivated to participate because in that trial they will receive a drug to potentially reduce these problems. Furthermore, the subset of 50 children that will be measured longitudinally comprises children participating in the DexaDays-2 randomized controlled trial based on the severity of their neurobehavioral problems. These patients will receive physiological dosages of hydrocortisone or placebo during a 5-day dexamethasone treatment, and the cross-over will take place after 2 courses of dexamethasone treatment. We do not know if this affects the occurrence of sarcopenia and physical frailty in this cohort, for example, whether children with dexamethasone-induced clinically relevant neurobehavioral problems also show more physical side effects. Besides, within the DexaDays-2 study patients aged 3-18 years were selected, which complicated selecting outcome measures suitable for all participants. We succeeded in selecting measurements that have previously been used and validated in pediatric populations indicating their usefulness; however, with the exception of the PedsQL-MFS, none of the measurements has been validated in pediatric oncology patients.

In conclusion, this study is designed to determine the occurrence and severity of sarcopenia and frailty components in children during the maintenance phase of ALL therapy, and to determine the effects of administration of high doses of dexamethasone on physical vulnerability. With this study we aim to create awareness about these potential risks in children with ALL, as well as expanding our knowledge for reducing further side effects.

## Abbreviations

ALL: acute lymphoblastic leukemia
CTCAE: Common Terminology Criteria for Adverse Events
DCOG: Dutch Childhood Oncology Group
ICC: intraclass correlation coefficient
PedsQL-MFS: Pediatric Quality of Life Inventory-Multidimensional Fatigue Scale
SMI: Skeletal Muscle Index
SMM: skeletal muscle mass
TRF: time to rise from the floor
TUG: Timed Up and Go Test
